## Abstract

**Study protocol:**

The optimal feeding for preterm infants during the first weeks is still debated, especially when mother’s own milk is lacking or limited. Intact bovine colostrum (BC) contains high amounts of protein, growth factors, and immuno-regulatory components that may benefit protein intake and gut maturation. We designed a pilot study to investigate the feasibility and tolerability of BC as the first nutrition for preterm infants. The study was designed into three phases (A, B, and C) and recruited infants with birth weights of 1,000–1,800 g (China) or gestational ages (GAs) of 27 + 0 to 32 + 6 weeks (Denmark). In phase A, three infants were recruited consecutively to receive BC as a supplement to standard feeding. In phase B, seven infants were recruited in parallel. In phase C (not yet complete), 40 infants will be randomized to BC or standard feeding. Feeding intolerance, growth, time to full enteral feeding, serious infections/NEC, plasma amino acid profile, blood biochemistry, and intestinal functions are assessed. This paper presents the study protocol and results from phases A and B.

**Results:**

Seven Danish and five Chinese infants received 22 ± 11 and 22 ± 6 ml·kg^−1^·day^−1^ BC for a mean of 7 ± 3 and 7 ± 1 days which provided 1.81 ± 0.89 and 1.83 ± 0.52 g·kg^−1^·day^−1^ protein, respectively. Growth rates until 37 weeks or discharge were in the normal range (11.8 ± 0.9 and 12.9 ± 2.7 g·kg^−1^·day^−1^ in Denmark and China, respectively). No clinical adverse effects were observed. Five infants showed a transient hypertyrosinemia on day 7 of life.

**Discussion and conclusion:**

The three-phased study design was used to proceed with caution as this is the first trial to investigate intact BC as the first feed for preterm infants. BC supplementation appeared well tolerated and resulted in high enteral protein intake. Based on the safety evaluation of phases A and B, the randomized phase C has been initiated. When complete, the Precolos trial will document whether it is feasible to use BC as a novel, bioactive milk diet for preterm infants. Our trial paves the way for a larger randomized controlled trial on using BC as the first feed for preterm infants with insufficient access to mother’s own milk.

## Introduction

Preterm birth (birth <37 weeks gestation) occurs in 10% of all pregnancies worldwide. Preterm infants suffer from various organ immaturities that may predispose them to immediate or later diseases. Adequate nutrient uptake and growth rates are required for very preterm infants to adapt well to postnatal life, but rapid enteral feeding is often difficult because the gastrointestinal tract is immature. Consequently, a suboptimal milk diet may lead to feeding intolerance, serious gastrointestinal complications (e.g., necrotizing enterocolitis, NEC), and late-onset sepsis (1).

Mother’s own milk (MM) is considered the optimal nutrition for preterm infants, and it is superior to infant formula (IF) in stimulating intestinal maturation, minimizing feeding intolerance, reducing the risk of NEC and infections, and improving long-term neurodevelopment (1). However, MM is sometimes not present in sufficient amounts or unavailable during the first days after preterm delivery. IF may be given as the first diet to supplement MM feeding, if donor milk (DM) is not available. Still, DM may remain less effective than MM to stimulate growth, secure adequate nutrient intake, and provide protection against NEC and infections (2–4). DM usually consists of pasteurized mature human milk (HM) obtained from mothers at a relatively late stage in lactation after giving birth at term. This means that DM contains a reduced amount of protein and bioactive components (5–7). DM is therefore not an ideal replacement for the first milk of the mother, the colostrum.

Bovine colostrum (BC) is the first milk from cows after birth, and we suggest that BC may be used to supplement MM during the first days of life, instead of IF or DM. BC is a rich source of protein and bioactive components, including lactoferrin, lysozyme, lactoperoxidase, immunoglobulins (Igs), as well as various growth factors (8, 9). Still, a number of nutritional characteristics of BC and milk differ from those in human colostrum (HC) and milk (e.g., levels of casein, whey proteins, oligosaccharides, and lactose). A number of phase I studies in human volunteers and phase II/III studies in patients have demonstrated a therapeutic potential of BC in gastrointestinal disorders (10). The safety and tolerability of BC has been tested in Danish pediatric patients subjected to intestinal resection (11) and chemotherapy for leukemia (NCT01766804). In a well-established piglet model of preterm infants (12), BC has repeatedly been shown to have beneficial effects in stimulating gut functions and resistance against NEC, relative to IF (13). When compared with DM and IF, BC promoted better postnatal growth, decreased diarrhea incidence, and increased brush border lactase activity in piglets (14). It is not yet clear, if the inferior quality of IF for preterm infants is due to its extensive industrial processing (e.g., heat treatment and fractionation) or suboptimal products (e.g., hydrolyzed whey proteins, vegetable carbohydrates, and vegetable oils). A general immunological hypersensitivity to bovine proteins in IF for preterm infants is unlikely, considering the overall low prevalence of cow’s milk allergy in infants (2–3%) (15).

On this background, we hypothesized that it may be feasible and justifiable to use intact BC as a supplement to MM during the first days of life, instead of DM or IF. Since BC has never been used as the first feed for preterm infants, we planned a three-phased pilot study to test the feasibility and tolerability in different clinical settings. The objectives of the pilot study were (1) to obtain the first information on whether BC used as the first nutrition is feasible and tolerable in preterm infants born between 1,000 and 1,800 g or 27 + 0 and 32 + 6 weeks’ gestational age (GA); (2) to help determine primary endpoints and sample size for a later, large randomized, controlled trial. Here, we report the entire study protocol and the results of the first two phases.

## Methods

### Study Design

Since this was the first time BC was given as the initial nutrition to preterm infants, the pilot study was designed into three phases (A, B, and C) to proceed cautiously (Figure 1). Furthermore, the study was performed in two countries with very different clinical settings to test the feasibility of giving the intervention both in a clinical setting with access to DM and early enteral feeding, and in a setting with no access to DM with later introduction of enteral feeding, representing the normal spectrum of enteral feeding practices across the world (16). In phases A and B, a stepwise, single-group design was used. Reconstituted BC was given as the first supplementary diet to MM for no longer than 10 days postnatal age. In phase A, three infants were included. Out of safety considerations, one infant was recruited and followed until he/she reached full enteral feeding and a weight gain of 15 g·day^−1^, before the next infant was recruited. Since no safety concern was raised in phase A, phase B was initiated, in which seven infants were recruited and studied in parallel. In phase C, a randomized, open labeled, and controlled trial design will be used. BC will be compared with the currently used supplementary diets to MM (IF and DM).

**Figure 1 F1:**
[figure not shown]
**Design of the three-phased Precolos pilot study**. BC is fed as the supplement (black boxes) when mother’s own milk is insufficient, instead of feeding donor milk (RH and HH) or infant formula (FWCH and SBMCH), according to local guidelines. In phase A, BC was given to three infants consecutively, i.e., each infant was followed until it reached full enteral feeding, and weight gain was 15 g·day^−1^ before the next infant was included. In phase B, BC was given to seven infants recruited in parallel. Phase C will be a randomized controlled trial (not yet completed). Due to differences in the normal progression of enteral feeding among hospitals, the BC intervention period was up to postnatal day 10 at RH and HH and will be up to postnatal day 14 for FWCH and SBMCH in phase C. BC, bovine colostrum; BW, birth weight; FWCH, Foshan Women’s and Children’s Hospital; GA, gestational age; HH, Hvidovre Hospital; PMA, postmenstrual age; RH, Rigshospitalet; SBMCH, Shenzhen Baoan Maternity and Child Healthcare Hospital.

### Study Sites

Two Chinese hospitals, Foshan Women’s and Children’s Hospital (FWCH, Foshan) and Shenzhen Baoan Maternity and Child Healthcare Hospital (SBMCH, Shenzhen), and two Danish hospitals, Rigshospitalet (RH, Copenhagen) and Hvidovre Hospital (HH, Copenhagen) participate in this pilot study. SBMCH and HH will only include patients for the randomized phase C.

### Inclusion Criteria

Inclusion criteria differ between the countries to reflect local clinical conditions.

FWCH and SBMCH:
○Preterm infants with birth weights between 1,000 and 1,800 g○Inclusion before first feedRH and HH:
○Preterm infants with GA between 27 + 0 and 32 + 6 wks○Inclusion before 24 h of ageBoth sites
○Delivered at the study site or transferred from other hospitals within 24 h after birth○Signed parental consent

### Exclusion Criteria

Major congenital anomalies or birth defectsCongenital infectionPerinatal asphyxia (umbilical or first neonatal pH ≤ 7.0)GA at birth <28 weeks (FWCH and SBMCH)Extremely SGA infant (weight SD score <−3 SD)Need for invasive mechanical ventilation or cardiovascular support before first BC feed

### Recruitment and Randomization

When a preterm infant was delivered, or transferred from other hospitals on the day of birth, attending neonatologists or a clinical researcher would evaluate the infant for its eligibility. If the infant fulfilled the recruitment criteria, the parent(s) would receive written and oral information about the study. Infants were included in the study after written parental consent was given.

Preterm infants were included in this study since we could not study the effect of BC as the first enteral nutrition for preterm infants by including other patient populations. Parents were informed with great care and given consideration time before inclusion. Because inclusion had to be done within a fixed period of time, this consideration time was not unlimited. If the parents found the consideration time to be too short, we accepted this and did not ask for consent.

No randomization was needed for phases A and B. For phase C, recruited infants are randomized into a control group and an intervention group in a 1:1 ratio. Random sequences of groups are generated by a computer program with randomly permuted blocks of sizes 2 and 4, written on slips, and put in opaque envelopes individually by an employee of the study sponsor. An envelope can only be opened to see the allocation after an infant has been enrolled. If multiple births are recruited together, all of them will be allocated to the same group, which will be accounted for during the data analysis. A set of 20 envelopes with random sequences will be generated for RH and HH together and coordinated by the primary investigator (PI) of RH *via* telephone call, and the recruitment will stop when 20 infants in total have been enrolled. The PI of HH will call the PI of RH when an infant is recruited and the PI of RH will open the corresponding envelope and tell which group the infant should be randomized to. For FWCH and SBMCH, two sets of 20 envelopes will be generated (one set for each) due to the difficulties related to coordination by telephone conversation. The study sponsor will coordinate and stop recruitment at the two Chinese sites when 20 infants in total have been enrolled.

### BC Intervention

The BC used in the study was prepared by mixing BC powder with cooled boiled water at room temperature (10 g powder in 50 ml water, 81kcal/100 mL). The BC powder was made from unmodified intact colostrum collected from healthy Danish dairy cows, obtained from the first and second milking after parturition. The BC was pasteurized (62.5°C for 30 min) and spray dried (ColoDan, Biofiber Damino, Gesten, Denmark). Reconstituted BC was kept in a refrigerator (4°C) for no more than 24 h. Prior to each feeding, the required amount of BC was warmed to 37°C in a water bath. The macronutrient and amino acid compositions of reconstituted BC are shown in Table 1 and are compared with that of HC, mature HM, and preterm IF.

**Table 1 T1:** **Macronutrient and amino acid compositions of human milk (HM), human colostrum (HC), and bovine colostrum (BC), and recommendations (17) for the concentrations of nutrients in preterm infant formula**.

	HM^a^	HC^a^	BC^b^	LSRO/ASNS
Carbohydrate (g·l^−1^)	67–78	44–59	33	9.6–12.5 (g·100kcal^–^^1^)
Lipid (g·l^−1^)	32–36	20–29	35	4.4–5.7 (g·100kcal^–^^1^)
Protein (g·l^−1^)	9–12	11–32	83	2.5–3.6 (g·100kcal^–^^1^)
Whey (g·l^−1^)	6–7.2	4.3–11.1	57	
Casein (g·l^−1^)	4–4.8	3.0–5.6	26	
**Amino acids (mg·g^−1^ protein)**				
Cysteine	20	40	16	34^c^
Histidine	23	23	26	21
Isoleucine	53	36	44	52
Leucine	104	91	90	102
Lysine	71	59	73	73
Methionine	16	13	19	See cysteine
Phenylalanine	37	43	45	78^c^
Threonine	44	55	59	45
Tryptophan	ND	ND^a^	19	15
Tyrosine	46	44	54	See phenylalanine
Valine	51	54	63	53
Arginine	36	55	41	29

*LSRO, Life Sciences Research Organization; ASNS, American Society for Nutritional Sciences*.

*^a^Values are based on Ref. (9, 18, 20); ND, not determined in the reference study*.

*^b^Carbohydrate, lipid, and amino acid compositions were calculated based on the product specifications of ColoDan BC powder provided by Biofiber Damino (Gesten, Denmark). Levels of whey and casein were measured at Department of Food Science (University of Copenhagen) by Milkoscan (FOSS, Hilleroed, Denmark) before and after casein removal*.

*^c^Methionine and cysteine, and phenylalanine and tyrosine are listed in combination. The ratio of each of these combinations of amino acids should not exceed 2:1 or 1:2 without appropriate testing for adequacy*.

### Nutritional Guidelines at RH and HH (Denmark)

All recruited infants were fed according to the nutritional guidelines for preterm infants at each site. At RH and HH, the ESPGHAN nutritional recommendations are generally followed (19). Enteral nutrition was introduced as soon as possible after birth (usually within 2–6 h) and for infants of more than 28 weeks GA, volumes were increased as much as the infants tolerated. Parenteral nutrition (PN) was provided from the first day of life to infants with a BW below 1,000 g and/or GA less than 28 weeks. Older infants did generally not get any PN. Full enteral feeding was defined as 160 ml·kg^−1^·day^−1^, and PN was used until the infant received ~90% of this volume. MM was the first choice of milk and only supplemented if not available in adequate amounts. Infants were supplemented with DM in the first weeks of life, before switching to IF (Enfalac Preterm Formula; Mead Johnson Nutritionals, Nijmegen, Netherlands). Fortification (Enfamil Human Milk Fortifier, Mead Johnson Nutrition) of MM and DM normally began when infants could take 140 ml·kg^−1^·day^−1^ enterally.

#### Nutritional Guidelines at FWCH and SBMCH (China)

At FWCH and SBMCH, feeding was normally initiated within 48 h after birth with a volume of 5–10 ml·kg^−1^·day^−1^ and advanced with a rate of 10–20 ml·kg^−1^·day^−1^. The volume of full enteral feeding was defined as 120 ml·kg^−1^·day^−1^, and supplementary PN was used until infants reached this volume. When MM was absent, or not available in adequate amounts, IF (SSC 81; Abbott Laboratories, Abbott Park, IL and Enfamil A+, Mead Johnson) was used. Fortification (Similac Human Milk Fortifier, Abbott Nutrition) of MM began when the infants could take 80 ml·kg^−1^·day^−1^ enterally.

#### BC Regimen

In phases A and B, BC was given as a supplement to MM to infants instead of DM (at RH) or IF (at FWCH) until postnatal day 10. The volume of BC fed each day was determined by the expected enteral feeding volume according to the above described nutritional guidelines at each hospital and the volume of MM available. Importantly, the volume of BC intervention together with available MM was not allowed to exceed a volume equivalent to 4.5 g·kg^−1^·day^−1^ protein, e.g., the upper protein intake limit according to ESPGHAN (19). When calculating the amount of protein provided by MM, 20 g·l^−1^ was used as the estimated concentration since preterm milk usually contains a higher amount of protein than normal term milk and out of safety concerns, we did not want to risk an underestimation of the protein intake from MM (20). If the available amount of MM, and the maximal volume of BC supplementation (due to protein limitations), could not meet the expected enteral feeding volume, DM (at RH) or IF (at FWCH) was given to fulfill the needs. After the intervention period, the infants received the standard enteral diets. In phase C, 40 infants will be randomized into two groups, an intervention group and a control group. Infants in the intervention group will receive BC, as described for phases A and B, and infants in the control group will receive the respective standard diets at each site. Infants in both groups will receive standard diets after the intervention period.

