The first 12 preterm infants in the world have now received intact BC as a supplement to MM during the first days of life. The high level of protein in BC might be an advantage, as the same volume of BC can supply about eight times more protein than HM and three times more than IF. For safety reasons, the maximal total protein intake was set at 4.5 g·kg^−1^·day^−1^ according to the ESPGHAN guideline, and plasma amino acid and blood biochemistry values for liver and kidney functions were recorded to monitor the protein metabolism. As expected, BC provided about 50% of the protein during the first week in phases A and B, resulting in a mean intake of 3.1 g·kg^−1^·day^−1^, a level that is often difficult to reach at this early stage (30, 31). Despite this, we still observed the common drop in weight *Z*-score from day 1 until a postmenstrual age of 37 weeks or discharge in these infants (32). Plasma amino acid levels were measured to monitor potential toxicity related to high protein intake. In phases A and B, a transient hypertyrosinemia was observed in five infants on days 6–8 when tyrosine levels normally reach a peak (33). Tyrosine levels returned to normal in all infants a week later. Prolonged high levels of tyrosine may be associated with later learning disability, as indicated from studies in term infants (34). IFs with a relatively high content of casein (60–80% of total protein) may also lead to increased phenylalanine and tyrosine levels (35). The casein intake was 0.6 g·kg^−1^·day^−1^, which was much less than that in the study referred above (1.4–1.9 g·kg^−1^·day^−1^) (35). Relative concentrations of phenylalanine and tyrosine in BC were similar to those in HM, and we did not observe elevated levels of phenylalanine. Thus, the blood biochemistry results did not raise any concerns of toxicity related to excessive protein intake. After consulting with our DSMB, we decided to continue with phase C where it will be possible to compare tyrosine levels in the BC group with those in a control group.

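### The 4.5 g/kg/day protein limit covers bovine colostrum plus mother's milk in the regimen, but total protein intake in the Discussion; the two cannot both hold, and phase C inherits the regimen rule

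*Protocol article*

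**What the plan says.** The operative rule is in the protocol article, BC Regimen: "the volume of BC intervention together with available MM was not allowed to exceed a volume equivalent to 4.5" g/kg/day of protein. The same sentence identifies 4.5 as the upper limit for protein intake in the nutritional guideline that the article cites. If MM plus the most BC that the limit permits falls short of the planned enteral volume, "DM (at RH) or IF (at FWCH) was given to fulfill the needs". The section does not say that this top-up counts towards the limit, and it names neither PN nor fortifier.

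The Discussion describes the same limit differently: "For safety reasons, the maximal total protein intake was set at 4.5" g/kg/day.

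For the MM part of the count, BC Regimen uses 20 g/l, which "was used as the estimated concentration since preterm milk usually contains a higher amount of protein than normal term milk". The stated aim is that "we did not want to risk an underestimation of the protein intake from MM". Table 1 gives protein as 9–12 g/l for mature human milk, 11–32 g/l for human colostrum and 83 g/l for reconstituted BC.

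The Chinese guideline section gives supplementary PN until 120 ml/kg/day is reached, and "Fortification (Similac Human Milk Fortifier, Abbott Nutrition) of MM began when the infants could take 80" ml/kg/day enterally. For phase C, BC Regimen says that the intervention group receives BC in the same way as in the first two phases.

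**The concern.** A limit on two sources is not a limit on the total. Under the regimen, whenever the limit stops further BC and volume is still needed, the infant receives more protein from a source outside the count. The Discussion nevertheless gives the limit to readers as a safety ceiling on total intake. That property does not follow from the rule that was applied.

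This matters because the study is a first use of BC as the initial feed, and the limit is the article's numerical control on protein exposure. The Safety Considerations section says that no stopping rules were defined. Phase C also adds two hospitals that took no part in phases A and B. Their staff would apply a limit whose scope is stated in two ways, and readers of the phase C results would not know which quantity had been held to 4.5.

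**Working it through.** **Reproducing the article's own figures.** Week-1 protein was 3.4 g/kg/day in 7 Danish infants and 2.7 in 5 Chinese infants (Initial Results). The weighted mean is (7 × 3.4 + 5 × 2.7)/12 = 37.3/12 = 3.11, which agrees with the 3.1 in the Discussion. BC protein at 22 ml/kg/day is 22 × 0.083 = 1.83 g/kg/day, against the reported 1.81 and 1.83. The 83 g/l from Table 1 is therefore the right input.

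**Where the limit binds.** Largest BC volume = (4.5 − 0.020 × MM volume)/0.083. With no MM this is 4.5/0.083 = 54.2 ml/kg/day.

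**What a top-up adds.** Total enteral protein with no MM = 4.5 + (enteral volume − 54.2) × top-up protein concentration. The inputs are:

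- DM at 9–12 g/l, taking it as mature human milk in Table 1.
- IF at 83/3 = 27.7 g/l, from the Discussion's statement that BC supplies about three times the protein of IF.
- As a second route, IF at 2.5–3.6 g/100 kcal (Table 1) and an assumed 81 kcal/100 ml. The article gives that energy density for BC, not for IF. It implies 20.3–29.2 g/l, which brackets 27.7.

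| Enteral volume (ml/kg/day) | Top-up (ml/kg/day) | Total with DM (g/kg/day) | Total with IF at 27.7 g/l (g/kg/day) |
|---|---|---|---|
| 60 | 5.8 | 4.55–4.57 | 4.66 |
| 80 | 25.8 | 4.73–4.81 | 5.21 |
| 100 | 45.8 | 4.91–5.05 | 5.77 |
| 120 | 65.8 | 5.09–5.29 | 6.32 |

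By the second IF route at 120 ml/kg/day: 65.8 × 0.81 = 53.3 kcal, times 2.5–3.6 g/100 kcal = 1.33–1.92 g, so the total is 5.83–6.42. For any other IF strength, the excess at 120 ml/kg/day is 0.0658 g/kg/day per g/l of protein. All totals leave out PN and fortifier.

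**Can the limit bind inside the BC period?** The Chinese guideline starts at 5–10 ml/kg/day and advances by 10–20 ml/kg/day. BC was started there on days 2–3. The fastest course is 10, 30, 50, 70 from day 2, which passes 54.2 on day 5. The slowest is 5, 15, 25, 35, 45, 55 from day 3, which passes it on day 8. Both fall within the 10-day window, and within the 14-day window for the Chinese sites in phase C (Figure 1 legend). This assumes no MM and no pauses in feeding.

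**The MM assumption.** 20 g/l lies between 11 and 32 g/l, close to the midpoint of 21.5. If true MM protein were 32 g/l, a BC + MM intake counted as 4.5 would be 4.5 + 0.012 × MM volume: 5.1 at 50 ml/kg/day of MM and 5.7 at 100. At 11 g/l it would be 4.5 − 0.009 × MM volume: 4.05 and 3.6. The error can run either way.

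**The case against.** The strongest reply is that one retrospective sentence in the Discussion is being set against an explicit rule in the Methods, so this is loose wording. The figures for 120 ml/kg/day also stack extremes: no MM, BC at its maximum, and that volume reached while BC is still given. Mean BC intake was about 22 ml/kg/day at both sites, well under half of 54. Time to 120 ml/kg/day at the Chinese site was 21 ± 8 days in Table 3 (22 ± 11 in the text), after the BC period. At the Danish site it was 8 ± 3 days, but the top-up there is DM, which adds less, and more MM was likely. Reported mean intakes were 3.4 and 2.7 g/kg/day in week 1 and 3.4 and 3.7 in week 2, all below 4.5. A condensed article may also leave the handling of PN and fortifier to the full protocol.

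Most of this stands as a limit on size. It does not remove the contradiction, because two stated sentences disagree whatever the full protocol adds, and the regimen itself directs the top-up. Group means do not show that no infant exceeded 4.5, since individual values are not given.

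Three stronger readings are tempting and are not supported:

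- A reader might infer that the limit was breached and that this explains the five cases of hypertyrosinemia among 12 infants. The article shows no breach and gives no such link; tyrosine was normal again on day 14.
- A reader might take 20 g/l to be below the colostrum range. It is inside it.
- A reader might take the article to claim that 20 g/l cannot underestimate MM protein. It states only an aim.

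**Conclusion.** The inconsistency holds. BC Regimen limits BC plus MM to 4.5 g/kg/day and adds uncounted DM or IF when that limit binds; the Discussion calls 4.5 the maximum for total protein. Phase C inherits the regimen rule.

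The direction of the excess needs only the limit to bind and some top-up to follow. Its size depends on volume: with no MM, from about 0.05–0.16 g/kg/day at 60 ml/kg/day to an illustrative maximum at 120 ml/kg/day of about 0.6–0.8 with DM or about 1.3–1.9 with IF. The IF range rests on the assumed 81 kcal/100 ml. These figures show what the rule permits; they do not estimate typical exposure.

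The 20 g/l assumption is a minor matter. Being below the upper end of the article's colostrum range, it does not by itself exclude underestimating MM protein in the first days.

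**What to change.** The sponsor should reconcile BC Regimen and the Discussion: state once which sources the 4.5 g/kg/day limit covers (BC and MM only, or all enteral and parenteral sources) and use that wording throughout, including the phase C instructions to sites. Which scope is right is a clinical decision that this review does not make. A sentence should set the 20 g/l assumption beside the colostrum range in Table 1.

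For phase C, derive each infant's daily protein from all enteral and parenteral sources in both arms, and report the number of days above 4.5 beside tyrosine and blood urea nitrogen. Nutritional intake is already a recorded outcome, and Figure 2 already splits protein by source, so no new data collection is needed.

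The cost is a wording change and one derived variable. The downside is that a stated safety property may look less favourable once total intake is shown.
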